#### Plans to give access to the full protocol, participant-level data and statistical code {31c}

Public access can be granted to the full study protocol, syntaxes or scripts, and the data dictionary once the study is completed, following reasonable request to the investigators. Furthermore, raw, preprocessed, and processed data essential to check study conclusions will be published in the digital archive Figshare once the outcomes are published.

### Oversight and monitoring

#### Composition of the coordinating center and trial steering committee {5d}

There will be multiple investigators of the coordinating center involved in the day-to-day support for the trial. They will meet to discuss matters associated with the trial on a regular basis and when needed.

#### Composition of the data monitoring committee, its role and reporting structure {21a}

The study will be monitored by the independent Clinical Monitoring Center (CMC) of Amsterdam UMC. Monitoring tasks that apply for this study are the enrolment progress, informed consent procedure, source data review and verification, safety reporting, and completeness of the trial master file and investigator site files. After every monitoring visit, a site monitoring visit report is written that provides an overview of all monitoring issues, findings, or discrepancies. The CMC clinical research associates involved in the monitoring process are independent from the study and study team and have no competing interests.

#### Adverse event reporting and harms {22}

All adverse events (AEs) reported spontaneously by the participant, their treating clinicians, or observed by the investigators will be recorded using a case report form (CRF). Serious adverse events (SAEs) will be reported to the sponsor without undue delay after obtaining knowledge of the event by the investigator. The sponsor will report the SAEs to the accredited Medical research ethics committee (METC) that approved the protocol, within 7 days of first knowledge for SAEs that result in death or are life-threatening followed by a period of a maximum of 8 days to complete the initial preliminary report. All other SAEs will be reported within a period of a maximum 15 days after the sponsor has first knowledge of the SAE.

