Participants will measure at three high-risk plantar regions per foot, including the previous ulcer location and two other regions where high in-shoe peak pressures are present, or where a pre-ulcerative lesion is present. The number of measurement sites can deviate from three if fewer or more high-risk regions are defined for a participant, as part of the personalized approach. A maximum of four high-risk regions is allowed to ensure practical feasibility and minimize treatment burden for participants. Foot temperature is measured once per day, preferably in the morning directly after getting out of bed. To facilitate measurement and assure adherence, the participant is advised to place the thermometer on a bedside table. If skin temperature measured in a region is ≥ 2.2°C higher than in the corresponding region on the contralateral foot, the temperatures are recorded in a logbook. If this above-threshold temperature difference is present for two consecutive days, a “hotspot” is present, and the participant is instructed to contact the research team. The research team will ask the participant about any swelling, change in color, change in structure, or drainage present at the hotspot and the use of their prescribed footwear. Based on these outcomes, the investigator may refer the participant for further diagnosis and foot care to their podiatrist. In any case, the participant will be instructed to decrease ambulatory activity with approximately 50% until the temperatures normalize (< 2.2°C temperature difference). If applicable, the participant will also be advised to increase the use of their custom-made footwear. If the temperature difference is larger than 4°C, or if temperatures do not normalize and are above threshold for four consecutive days, the participant will be referred immediately by the podiatrist. If needed, direct referral for treatment to specialized care will take place. This may involve, among other things, immobilization of the foot.

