Following randomization, four specific follow-ups are scheduled for patient education that includes motivational interviewing, and will be conducted by one of the senior investigators who are trained in motivational interviewing methods by an expert psychologist (FU, see Fig. 1). The first follow-up is by telephone, 1 week after randomization. When participants are non-adherent to wearing their custom-made footwear, defined as an average wearing time < 8 h/day, the education will focus on changing behavior to increase adherence, using motivational interviewing (see below). For participants who are adherent to wearing their custom-made footwear, the education will focus on retaining this desired behavior. The next three follow-ups will take place 1 week after each regular 3-monthly study visit and will also be conducted by telephone. For these follow-up interviews, the personalized FFTT model will be updated with outcomes of in-shoe pressure, physical activity, and wearing time measurements, collected at each regular study visit. These outcomes will be discussed during the interviews, together with the self-care behavior of the participant. All follow-ups for education will contain motivational interviewing, that is provided in accordance with a protocol developed for the study and based on published protocols on motivational interviewing to improve footwear adherence [26]. If adherence to footwear use, temperature monitoring, or self-care is high, motivational interviewing will focus on retaining this desired behavior; if adherence is low, motivational interviewing will focus on behavior change. All telephone conversations will be recorded and a random subset will be analyzed for treatment fidelity, scored using the Motivational Interviewing Treatment Integrity (MITI 4) code [43].

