##### Assessments during follow-up

Each participant will be followed for 12 months. If a participant has a foot ulcer at 12 months, they will be followed for another 6 months or until healing, whichever comes first. Follow-up will take place after 3, 6, 9, and 12 months (FU3, FU5, FU7, and Final visit (FV), respectively). Prior to each regular study visit, all participants will receive the EQ-5D-5L questionnaire and study specified versions of the iMTA iMCQ and iMTA iPCQ to gather volume data on medical costs, family costs, and productivity loss [45]. Additionally, at 6 and 12 months, all participants also complete the study questionnaire (see the section “Assessments at baseline visit”), and at 12 months also the SF-36. Participants in enhanced therapy will hand in their weekly diaries.

Custom-made footwear wearing time will be assessed during each 3-monthly visit by reading out the OrthoTimer sensor in the shoe. At 6 and 12 months, physical activity is assessed by wearing the activity monitor for 1 week. At 12 months, barefoot and in-shoe plantar pressure measurements will be repeated. Use of intramural healthcare resources during the study will be obtained at final visit from the participants’ medical status. If a participant has a foot ulcer at 12 months, visits will be scheduled at 15 and 18 months, or 2 weeks after healing (whichever comes first). During these visits, volume data on medical costs, family costs, and productivity loss will be gathered (iMTA) and the EQ-5D-5L will be completed. An overview of all measurements can be seen in Fig. 2.

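### Adverse events are captured only passively while the enhanced arm has twice the scheduled study contacts, so recorded non-serious events may be inflated in that arm

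*Protocol article*

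**What the plan says.** The section Adverse event reporting and harms {22} of the protocol article gives the capture rule: "All adverse events (AEs) reported spontaneously by the participant, their treating clinicians, or observed by the investigators will be recorded". The article describes no adverse-event question put to all participants at set times.

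Contacts after randomisation differ by arm:

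- **Both arms** (Assessments during follow-up): "Follow-up will take place after 3, 6, 9, and 12 months (FU3, FU5, FU7, and Final visit (FV), respectively".
- **Enhanced therapy only** (Intervention description {11a}, personalized education): "Following randomization, four specific follow-ups are scheduled for patient education that includes motivational interviewing". On timing: "The first follow-up is by telephone, 1 week after randomization", and "The next three follow-ups will take place 1 week after each regular 3-monthly study visit and will also be conducted by telephone".
- **Enhanced therapy only** (Assessments during follow-up): "Participants in enhanced therapy will hand in their weekly diaries".
- **Enhanced therapy only** (Intervention description {11a}, temperature monitoring): when a hotspot is found, "the participant is instructed to contact the research team", and then "The research team will ask the participant about any swelling, change in color, change in structure, or drainage present at the hotspot".

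The same temperature-monitoring text has the participant's experience with the measurements discussed at each study visit, so even the shared visits differ in content. Who will be blinded {17a} states that participants, shoe technicians and investigators cannot be blinded.

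**The concern.** Passive capture gives comparable counts only if the opportunities to mention or notice an event are similar in both arms. Here they differ by design, and the people who report and record events know the allocation. The hotspot calls go further, because they are solicited questioning about the feet in one arm only.

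The events at stake are the minor ones that new footwear or altered walking could plausibly cause: blisters, skin lesions, musculoskeletal complaints. The protocol itself treats burden and harm as open questions. The Introduction mentions over-diagnosis from false-positive temperature readings, and the indoor-footwear text has potential harms discussed with the participant. If more such events are recorded under enhanced therapy, a reader cannot tell a real harm from an effect of contact. A false signal could impede adoption, and a true one could be dismissed as extra contact.

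**Working it through.** The protocol states no adverse-event rate, contact ratio or power for harms, so there is no figure of its own to reproduce.

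**Step 1. Count scheduled contacts after randomisation.**

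- Usual care: visits at 3, 6, 9 and 12 months = 4.
- Enhanced therapy: the same 4 visits + 4 calls (week 1, and one week after each of the 3, 6 and 9-month visits) = 8.
- Ratio 8/4 = 2.0. Adding the baseline and randomisation visits gives 10/6 = 1.67, but those precede treatment. In-person 3-monthly visits are equal, 4 and 4.

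**Step 2. Ask how much extra calendar time the calls cover.** Three calls follow a shared visit by one week, so they overlap with it heavily. As an assumption, suppose an event is mentioned only if a contact follows within 4 weeks.

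- Usual care: 4 × 4 = 16 weeks.
- Enhanced therapy: 3 × 5 (visit plus call a week later) + 4 (final visit) + 1 (week-1 call) = 20 weeks.
- Ratio 20/16 = 1.25. Doubling the contacts does not double the coverage.

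**Step 3. Allow for routes common to both arms.** Assumptions, none taken from the document:

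- the true event rate is the same in both arms, and timing is uniform over 12 months;
- each contact within w months after the event (w = 1 or 3) brings it out with probability c (0.2, 0.5 or 0.8);
- a route common to both arms, such as treating clinicians or records, captures it with probability b (0, 0.5 or 0.9).

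With k contacts in the window, the probability of being recorded is 1 − (1 − b)(1 − c)^k, averaged over event times. Contacts are at 3, 6, 9 and 12 months in usual care, and at 0.25, 3, 3.25, 6, 6.25, 9, 9.25 and 12 months in enhanced therapy. Diaries and hotspot calls are left out. The months of event time with each k are:

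| Window | Usual care | Enhanced therapy |
|---|---|---|
| 1 month | k=1: 4; k=0: 8 | k=1: 2.75; k=2: 2.25; k=0: 7 |
| 3 months | k=1: 12 | k=1: 2.75; k=2: 9.25 |

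Worked case at the high end (w = 1, c = 0.2, b = 0):

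- usual care 4 × 0.2/12 = 0.0667;
- enhanced (2.75 × 0.2 + 2.25 × 0.36)/12 = 0.1133;
- ratio 1.70.

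Worked case near the low end (w = 3, c = 0.5, b = 0.9):

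- usual care 1 − 0.1 × 0.5 = 0.950;
- contact capture in enhanced therapy is (9.25 × 0.75 + 2.75 × 0.5)/12 = 0.6927, so recorded 1 − 0.1 × 0.3073 = 0.969;
- ratio 1.02.

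All cases, ratio of recorded events (enhanced/usual), given as 1-month / 3-month window:

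| c | b = 0 | b = 0.5 | b = 0.9 |
|---|---|---|---|
| 0.2 | 1.70 / 1.62 | 1.04 / 1.10 | 1.01 / 1.01 |
| 0.5 | 1.53 / 1.39 | 1.08 / 1.13 | 1.01 / 1.02 |
| 0.8 | 1.36 / 1.15 | 1.08 / 1.07 | 1.01 / 1.01 |

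The true event rate cancels from these ratios.

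**Step 4. Chance of a spurious significant excess.** With 63 per arm (126 in total, Sample size {14}), an assumed true event proportion of 40% and a two-sided 5% test, the largest value is about 17%. It arises at w = 3, c = 0.5, b = 0, where 20.0% and 27.7% of participants have a recorded event. With b = 0.9 it is about 3%, close to the 2.5% expected in that direction by chance alone.

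**The case against.** The strongest reply is that much of what matters is already collected in the same way in both arms.

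- Treating clinicians are named in the rule as a source, and Explanation for the choice of comparators {6b} describes foot care every 1 to 3 months for everyone.
- Falls are a secondary outcome. Medical consumption and productivity loss are asked of all participants before each 3-monthly visit. Intramural care is taken from records at the final visit. Footwear use and usability are asked of all at baseline, 6 and 12 months. Ulcer photographs go to a blinded panel.

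This stands, and it confines the point to non-serious events outside those outcomes. It does not remove the point. Clinicians' reporting of such events is also spontaneous; the instruction to inform the investigator at once concerns ulcers. The questionnaires are not adverse-event forms.

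Other replies have some force. Adverse events are not among the listed outcomes, and the article states no between-arm test of them, so no stated analysis is wrong. Diaries are described as reminders and for self-reported adherence, not for harms. The visit-specific case report forms and Fig. 2 are not shown, so a prompt on a form cannot be excluded, although a rule built on spontaneous reports points the other way. The likely bias runs against the intervention and touches none of the three primary outcomes.

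A reader might infer that harms in general will appear more frequent under enhanced therapy, or about twice as frequent because contacts are doubled. The document supports neither. The calls mostly fall just after a shared visit, and common routes can shrink the difference to almost nothing. Nor does the text fix a separate footwear visit that could be added to the count: it says only that indoor-footwear production generally takes six weeks, and participants may decline it.

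**Conclusion.** The point holds in a limited form. Followed as written, the rule gives unequal ascertainment of non-serious adverse events, and the expected direction is more recorded events under enhanced therapy. The facts behind it are in the text: passive capture, 8 against 4 scheduled contacts after randomisation, diaries and hotspot questioning in one arm, and unblinded participants and investigators.

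The size is not derivable from the document. In the model above, the ratio with no true difference is 1.01 to 1.02 with 90% common background capture, 1.04 to 1.13 with 50%, and 1.15 to 1.70 with none. The protocol gives no basis for choosing among these. The result is therefore a possible inflation, ranging from negligible to substantial. It is worth correcting because the remedy is cheap, but it does not threaten the primary outcomes.

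**What to change.** Four changes to data collection and reporting:

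1. At the 3, 6, 9 and 12-month visits, ask every participant in both arms the same short adverse-event question covering the time since the last visit, in fixed wording.
2. Add a field to the case report form for how each event came to light: common question, clinician, education call, diary, hotspot call or other.
3. Base any between-arm comparison on events elicited at these common visits plus serious adverse events. An event first mentioned on a call still counts if the participant reports it again when asked at the next visit.
4. List events learned only through education calls, diaries or hotspot calls separately.

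The cost is a few form items at visits already held, with no extra visit or staff. The downsides are that more minor events will be recorded in both arms, and that solicited data will be incomplete for participants already past a visit. The latter matters because Trial status reports that recruitment began in February 2022. If the change comes late, the source field still allows a like-for-like sensitivity comparison for the remaining follow-up. The question does not remove reporting bias from unblinded participants; it only equalises the opportunity to report.

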#### Frequency and plans for auditing trial conduct {23}

Given the monitoring plan, no audits are planned.

#### Plans for communicating important protocol amendments to relevant parties (e.g., trial participants, ethical committees) {25}

All amendments to the protocol will be reported to and assessed by the Medical Ethics Review Committee of Amsterdam UMC. Participants will be notified when amendments are substantial according to the Medical Ethics Review Committee.

#### Dissemination plans {31a}

All outcomes will be published in peer-reviewed publications and presented at scientific conferences. Associated healthcare professionals and companies will be informed about the results as soon as possible after finishing the trial. Furthermore, an implementation committee consisting of patient representatives, healthcare professionals, and an implementation expert is already involved in the trial to discuss and prepare implementation strategies after the trial results are obtained.

## Discussion

The DIASSIST trial aims to assess the effect of an integrated personalized assistive devices approach aimed to help prevent foot ulcer recurrence in people with diabetes on effectiveness, treatment adherence, and cost-utility. We designed this intervention and this RCT using a multidisciplinary systematic design approach, that consisted of the following steps: (i) systematic literature search and assessment of available evidence; (ii) assessment of clinical guidelines; (iii) first design of the intervention; (iv) multidisciplinary discussions with patients, healthcare professionals, and researchers; (v) testing the design with patients; and (vi) final design of the intervention. In this discussion, we will describe the considerations and outcomes of these steps.

### (i and ii) Assessment of evidence and guidelines

We systematically searched the literature for proven interventions that help prevent diabetic foot ulceration. We identified the four modalities as described in the “Interventions” section to be relevant to include in our design process. Results of these previous studies indicated a positive effect of the interventions, especially when treatment adherence is high [10, 14, 15, 21]. In addition to the 29 publications about single modalities as referenced in the “Interventions” section, we identified three studies that assessed a form of integrated care [71–73]. However, none combined all the abovementioned single interventions. We built upon the concept of integrated care from these studies by combining multiple interventions and expanded this concept by combining more and different modalities and using a personalized approach.

We subsequently assessed international clinical guidelines on current recommendations for the prevention of plantar foot ulcer recurrence [7]. Three modalities, i.e., custom-made footwear, daily at-home monitoring of foot temperatures, and patient and family education, are included in the guidelines, but these are not, or not according to a state-of-the-art protocol, implemented in clinical practice. Custom-made footwear specifically for indoor use is a new treatment, and as such not recommended in guidelines [7]. In addition, although there is no scientific evidence yet, there is a strong recommendation in the guidelines to integrate these treatments.

### (iii–v) First design, multidisciplinary discussions, and pilot testing

Combining the outcomes from previous trials and the guideline recommendations with our clinical experience, we designed the first version of our state-of-the-art integrated approach. The approach is designed to assess patients who are at high risk for developing a plantar foot ulcer and who are expected to benefit from the combined modalities. We therefore decide to exclude patients who have had an ulcer on the apex of their toes as the only ulcer location in the last 4 years up until inclusion. For these patients, a flexor tendon tenotomy would likely be a better first treatment option than the combination offered in this trial [7, 30]. Patients with a bilateral amputation proximal to the Chopart joint are also excluded, since the primary working mechanism of the intervention is aimed at reducing plantar foot ulcer recurrence by optimizing footwear and footwear adherence, and both are not applicable to these patients.

The first design of the intervention was then discussed during multiple meetings with a total of 22 experts from different disciplines. This included specialists from rehabilitation and internal medicine, shoe technicians, podiatrists, researchers, and patient representatives. In addition, we discussed the design with an independent advisory board of seven members representing a variety of expertise, including internal medicine and vascular surgeon specialists, representatives of the Dutch podiatry association (NVvP), a patient representative from the Dutch Diabetes Association (DVN), and an implementation expert of Amsterdam UMC. This committee will also continue to meet on a yearly basis to be informed about trial progress, and to discuss future implementation. Given the extensive involvement of multiple stakeholders, we expect that implementation of the integrated and personalized approach will be facilitated, provided it is successful.

The approach was tested in three people with diabetes at high risk of ulceration, who were given the opportunity to provide feedback on the design and their experiences. Testing included the production of custom-made indoor footwear, the patient education model, and the trial visit procedures. Based on the discussions with experts, the implementation committee, and patient representatives, minor adjustments were made before finalizing the design. These adjustments were mainly related to the visual feedback and communication towards participants using the personalized FFTT model. We also adapted the first visit for patient education after the evaluation of the first participants in the RCT. This visit was originally scheduled 6 weeks after randomization, to provide feedback on footwear adherence as measured at baseline. However, the indoor footwear was provided in that first 6-week period, which made the feedback on treatment adherence outdated, resulting in confusion with the participants. The first visit for patient education was therefore rescheduled to 1 week after randomization, as described in the “Participant timeline {13}” section.

